3) an earlier start of both specific physical and psychosocial treatment provided by a multidisciplinary team;

4) early individual goal setting;

5) early start of psychological and social counselling;

6) an integrated co-ordination of treatment between the trauma surgeon and the rehabilitation physician, and

7) a shorter stay in a trauma rehabilitation unit

may be more (cost-) effective. Such SFTRS approach may lead to less secondary complications associated with immobilisation, which would negatively influence recovery and quality of life. Early personalised goal setting and early treatment of depression are known to positively affect outcome. SFTRS may lead to faster reintegration into society. Early return to work and active support from the multidisciplinary rehabilitation team will lead to a more stable social network, and the patient becoming less reliant on professional care in the long term. Also, the SFTRS may reduce the length of stay of multi-trauma patients in a hospital. Furthermore, earlier rehabilitation treatment in a specialised rehabilitation unit may also reduce the length of stay in the rehabilitation clinic, thus reducing costs of hospital/clinic consumption. At this moment it is not possible to make a precise calculation of these savings. Since earlier discharge also means that patients take part in society and work earlier, costs related to production losses and patient & family costs are expected to be lower.

The main objective of this study is to examine the effectiveness, costs and cost-effectiveness of an integrated care service for multi-trauma patients, called 'Supported Fast track multi-Trauma Rehabilitation Service' or SFTRS.

The general research question is:

Which of 2 rehabilitation services, i.e. 'Conventional multi-Trauma Care Service' (CTCS) or 'Supported Fast track multi-Trauma Rehabilitation Service' (SFTRS), is most (cost-) effective from a societal point of view?

Sub-questions are:

- What are the effects of the SFTRS on generic quality of life in multi-trauma patients as compared to the CTCS?

- What are the effects of the SFTRS on functional health status as compared to the CTCS?

- What are the costs to health care and to society of the SFTRS as compared to the CTCS?

- What is the cost-effectiveness of the SFTRS as compared to the CTCS?

The general hypothesis of this study is that SFTRS is more (cost-) effective than CTCS.

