### Interventions/services

Supported Fast track multi-Trauma Rehabilitation Service

SFTRS involves the following:

a) The rehabilitation physician from the rehabilitation centre is routinely involved at a very early stage post-trauma. This allows an early start for multidisciplinary rehabilitation treatment;

b) Early transfer (within five days after having been added to the waiting list from the rehabilitation centre) to a centralised, specialised trauma rehabilitation unit equipped with facilities for early training programs;

c) Early individual rehabilitation goal setting;

d) Close co-operation and exchange of views and experiences between the trauma surgeon and the rehabilitation team by, for example, monthly clinical sessions and individual patient visits by the trauma surgeon in the first weeks after discharge;

e) Well-documented treatment protocols for multi-trauma patients for both the hospital and rehabilitation centre phases.

Three phases can be identified in the treatment of multi-trauma patients:

1 Early rehabilitation phase

2 Stage II rehabilitation phase

3 Discharge or post-discharge phase

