### Demographic and medical variables

Upon arrival at the A&E (= T0) the following variables will be recorded: age, gender, medical history, mediation usage, diagnosis, ISS score, date and time of trauma and Glasgow Coma Scale (GCS).

As soon as possible post-injury the following data are collected: trauma treatment, possible complications (description, number and extend) and time in hospital. The following additional data are recorded upon admission in the rehabilitation centre: individual rehabilitation treatment aims, pre-trauma psychosocial status and pre-trauma employment status.

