### Statistical analyses

In non-randomised comparative studies, variations in case mix between centres can influence the interpretation of outcome data [48]. Therefore, for each of the data sets collected at T1 through T4, differences in outcome variable between the 2 services will be tested using multiple MANCOVA's, entering various indicators of case mix as co-variates, i.e. age, gender, ISS, number of complications, pre-trauma psycho-social status.

When patients drop out of the study, the reason for their withdrawal will be recorded. Drop-outs may bias the treatment effect evaluations. Therefore, the following regime will be applied:

- Missing T4 measurement: 'last-observation-carried-forward' principle will be applied.

- Missing T3 or T2 measurement: linear interpolation of data using data from adjacent time points (e.g. T1 and T4) for imputation.

- Missing T0 or T1 measurement or more than 2 missing measurements: discarding of patient data and influx of additional patient in order to meet n = 82 per group.

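### The main model adjusts for number of complications with no time cut-off, so it can remove part of the effect that SFTRS is meant to have

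*Protocol article*

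**What the plan says.** All statements are from the protocol article.

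- **Statistical analyses.** Because the study is not randomised, the section plans that "for each of the data sets collected at T1 through T4, differences in outcome variable between the 2 services will be tested using multiple MANCOVA's". The adjustment in these models is described as "entering various indicators of case mix as co-variates, i.e. age, gender, ISS, number of complications, pre-trauma psycho-social status". The section gives no time window for the complications and describes no between-service test without them.
- **Introduction.** "Such SFTRS approach may lead to less secondary complications associated with immobilisation, which would negatively influence recovery and quality of life". The research question that follows asks which of the two services is more (cost-)effective.
- **Demographic and medical variables.** The list recorded on arrival at A&E is "age, gender, medical history, mediation usage, diagnosis, ISS score, date and time of trauma and Glasgow Coma Scale (GCS"). Complications are not in it. They come in the next sentence: "As soon as possible post-injury the following data are collected: trauma treatment, possible complications (description, number and extend) and time in hospital".
- **Interventions/services.** Under SFTRS, "The rehabilitation physician from the rehabilitation centre is routinely involved at a very early stage post-trauma", and the service includes "Well-documented treatment protocols for multi-trauma patients for both the hospital and rehabilitation centre phases".
- **Primary outcome measures.** Complications are mentioned, with injury severity, among the things on which quality of life and functional recovery depend.

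**The concern.** A case-mix covariate should describe how the patients differed before the services could act on them. Age, gender and ISS are fixed at injury. Pre-trauma psychosocial status is recorded later, on admission to the rehabilitation centre, but refers to the time before injury. The number of complications has no such anchor. It is collected beside length of hospital stay, and SFTRS is designed to alter the hospital phase.

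If SFTRS prevents complications, and complications worsen FIM and SF-36 scores, the complication count lies on the causal path. Holding it constant compares patients with equal numbers of complications, so SFTRS gets no credit for those it prevented. There is a second risk. If unmeasured severity drives both complications and outcome, conditioning on complications links service to severity within each complication level and distorts even the remaining direct effect.

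The covariate enters the only between-service outcome test that the article describes, for both primary outcomes and at every follow-up point. The Discussion ties the result to nation-wide introduction, so a real benefit reported as small or absent would matter.

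**Working it through.** **1. Is each link of the pathway in the article?**

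| Link | Where | What it supports |
|---|---|---|
| SFTRS → fewer complications | Introduction | Stated as possible, for complications of immobilisation |
| Complications → worse outcome | Introduction; Primary outcome measures | Stated |
| SFTRS active while complications accrue | Interventions/services | Early involvement; protocols for the hospital phase |
| Count limited to the time before SFTRS acts | Demographic and medical variables; Statistical analyses | Not stated |

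**2. The plan's own figure.** Inputs from the Population section: reference improvement 30.2 motor FIM points, target 15% of it, SD 9.5, two-sided alpha 0.05, power 80%.

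- Target difference: 0.15 × 30.2 = 4.53 points.
- Normal formula: n = 2 × [9.5 × (1.960 + 0.842) / 4.53]² = 69.04, so 70 per group. The t-test version gives 70.01, so 71, as stated.

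This sample size does not depend on the covariate and is not in dispute.

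**3. Effect of blocking the pathway.** Let f be the share of the total effect that runs through the counted complications. The documents give no value, so f is an assumption. The adjusted model targets 4.53 × (1 − f). With SE = 9.5 × √(2/71) = 1.594, power = Φ(4.53 × (1 − f) / 1.594 − 1.960). The last column is the evaluable number per group that restores 80% power under the normal formula.

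| f | Effect left (points) | Power at 71 per group | n per group for 80% |
|---|---|---|---|
| 0 | 4.53 | 81% | 70 |
| 10% | 4.08 | 72% | 86 |
| 20% | 3.62 | 62% | 108 |
| 30% | 3.17 | 51% | 141 |
| 40% | 2.72 | 40% | 192 |
| 50% | 2.26 | 29% | 277 |

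SD is held at 9.5. A covariate related to outcome would reduce the residual SD, but the documents give no correlation. To offset f = 10% in power, it would have to remove 1 − 0.9² = 19% of the residual variance; for f = 30%, 1 − 0.7² = 51%. That would restore power but not the missing part of the estimate.

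**4. Simulation check, all inputs assumed.** Mean of 1.5 complications under CTCS, 3 FIM points lost per complication, total effect 4.53, residual SD 8. In the last column an unmeasured severity factor costs 3 FIM points per SD and raises the log complication rate by 0.4 per SD.

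| SFTRS cuts complications by | Without covariate | With covariate | With covariate, unmeasured severity present |
|---|---|---|---|
| 0% | 4.50 | 4.51 | 4.55 |
| 20% | 4.53 | 3.63 | 3.35 |
| 30% | 4.56 | 3.19 | 2.70 |

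At a 20% cut, the mediated part is 0.2 × 1.5 × 3 = 0.9 points and the direct effect is 4.53 − 0.9 = 3.63. The covariate model returns that figure, and less when severity is unmeasured. With no effect on complications, the models agree.

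**The case against.** Four points deserve weight.

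- **Timing is ambiguous.** Complications are to be collected as soon as possible after injury, and the Data collection section describes baseline (T0) in the same terms, while the variables section ties T0 to arrival at A&E. On one reading, complications are baseline data. However, time in hospital, in the same sentence, cannot be complete at baseline, and no cut-off is given. This objection removes certainty, not the problem.
- **Two kinds of complication.** The Introduction speaks of complications of immobilisation. The recorded count may include injury or surgical complications that precede any effect of rehabilitation. Those are legitimate case mix, and this part of the objection stands.
- **Dropping the covariate has a price.** The two centres are about 150 km apart and patients are not randomised. If early complications differ between the regions for reasons unrelated to the service, omitting them leaves confounding of unknown direction. This also stands, and the fix must address it.
- **An article condenses.** The time window may be defined in the full protocol or SAP. But the article positively names an unrestricted count as a covariate; the point rests on what is written, not on an omission.

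A reader might infer that the variable is a mediator throughout and that the trial will certainly understate SFTRS by a known amount. The article does not support this. It says only that SFTRS may reduce such complications, and it gives neither the mediated share nor the timing of the counted events.

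**Conclusion.** The point holds in conditional form. As written, the main analysis conditions on a count that can include events the service is intended to prevent. To the extent that it does, the estimate is not the total effect that the research question asks for, and under the authors' own hypothesis it is biased toward no difference.

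The size cannot be settled from the documents. It is zero if SFTRS does not change the counted complications. The illustrated fall in power from 81% to between 72% and 29% rests on an assumed mediated share of 10% to 50%, SD 9.5, 71 evaluable patients per group and no precision gain. It concerns FIM at T1 only; the article gives no planning figure for SF-36. Bias from unmeasured severity is plausible, but its size here comes only from assumed inputs.

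**What to change.** In Statistical analyses, remove the number of complications from the covariate list of the main model. Keep age, gender, ISS and pre-trauma psychosocial status, whose values the service cannot change.

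Complications may stay in the main model only if restricted to those arising before the service can act. That start point must be defined in the same way for both regions.

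Report later complications by service as an outcome. Give the complications-adjusted model as a labelled sensitivity or mediation analysis.

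Cost: removal is a one-line change and needs no new data. The restricted version needs the timing of each complication; the article lists their description, number and extent, but not dates. The downside of removal is some residual confounding if early, pre-service complications differ between the regions. Showing the adjusted model beside the main one would reveal how far the conclusion depends on this, although a gap between the two could reflect mediation as well as confounding.

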To date, no exact data on differences in quality of life outcome between different treatment services for multi-trauma patients are available. Czyrny and co-workers [14] report an improvement in motor FIM score of 30.2 in a small group of bilateral lower limb multi trauma patients having received both hospital and subsequent rehabilitation treatment, at a mean length of stay of 62.8 (+/-6.0) days. In order to detect a difference of 15% of such improvement in FIM score between SFTRS and CTCS at T1 (assuming a two-sided significance level of 0.05, a power of 80%, and a common standard deviation (sd) of 9.5 as reported by Czyrny [14]), 71 persons per group are needed. Taking into account a 15% loss to follow-up, the required sample size is 82 persons per group (164 persons in total).

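### Discarding and replacing patients who miss T0, T1 or more than two measurements makes the analysis set depend on a post-treatment visit, and allows twice for the same loss

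*Protocol article*

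**What the plan says.** The Statistical analyses section of the protocol article warns that drop-outs can bias the comparison and then sets three rules:

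- "Missing T4 measurement: 'last-observation-carried-forward' principle will be applied".
- "Missing T3 or T2 measurement: linear interpolation of data using data from adjacent time points", with T1 and T4 given as an example.
- "Missing T0 or T1 measurement or more than 2 missing measurements: discarding of patient data and influx of additional patient", continuing until each group has 82.

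The completed data go into separate covariate-adjusted MANCOVAs at each of T1 to T4. The covariates are age, gender, ISS, number of complications and pre-trauma psychosocial status.

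The Data collection section puts T0 as soon as possible after injury and T1 to T4 at 3, 6, 9 and 12 months. The sample size in the Population section is set for T1: "In order to detect a difference of 15% of such improvement in FIM score between SFTRS and CTCS at T1". It arrives at "71 persons per group are needed" and then adds an allowance: "Taking into account a 15% loss to follow-up, the required sample size is 82 persons per group (164 persons in total".

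The only sensitivity analyses described concern costs (Determination of costs).

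**The concern.** A rule meant to limit drop-out bias should not choose patients by something measured after treatment has begun. Here a patient stays in the analysis only if T1 was obtained and at least one later visit exists. By T1 the services have diverged. The Interventions section describes early transfer to one centralised unit under SFTRS. Under CTCS, patients may go on to outpatient clinics, rehabilitation centres, nursing homes, GPs or local physiotherapists. The chance of being measured at T1 could therefore differ by service. Recruiting a substitute restores the count, not the population first enrolled.

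The rule governs both primary outcomes at every visit. The Discussion says the results should show whether the new service ought to be introduced nation-wide.

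**Working it through.** **1. Reproducing the plan's sample size.** Inputs from the Population section: "an improvement in motor FIM score of 30.2", a target of 15% of it, and "assuming a two-sided significance level of 0.05, a power of 80%, and a common standard deviation (sd) of 9.5".

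- Target difference: 0.15 × 30.2 = 4.53 points.
- Normal approximation: n = 2 × (1.960 + 0.842)² × (9.5 / 4.53)² ≈ 69.0, giving 70. The noncentral t calculation gives 71 (power 79.99% at 70, 80.6% at 71). The stated 71 is reproduced.
- Allowance for loss: 71 × 1.15 = 81.65, giving 82, as stated. Dividing instead, 71 / 0.85 = 83.5, would give 84, a minor difference.

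**2. Loss allowed for twice.** The 82 is meant to be enrolled so that about 71 remain. The missing-data rule instead makes 82 the number retained. At 15% discarded, 82 / 0.85 = 96.5, so about 97 are enrolled per group and 97 − 82 = 15 deleted. Over an assumed 5% to 30% discarded, enrolment is about 87 to 118 per group.

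**3. What the third criterion means.** There are five measurements, T0 to T4. A patient missing T0 or T1 is already out. For anyone else, more than two missing can only mean that T2, T3 and T4 are all missing. Such a patient has an observed T1 outcome, at the visit the study is sized on, and the rule removes it from the T1 comparison. Likewise, a missing T0 removes every observed follow-up outcome.

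**4. Size of the selection effect at T1 (assumed scenarios; the article gives no loss by service).** If the worst fraction p of a normal outcome is removed, the retained mean rises by φ(z_p) / (1 − p) standard deviations.

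- p = 0.15: 0.274 SD. p = 0.05: 0.109 SD. Difference 0.166 SD.
- 0.166 × 9.5 ≈ 1.6 points with no true effect, 35% of 4.53.
- If being discarded correlates only 0.5 with outcome, the effect halves to about 0.8 points (17%).

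A simulation with no true effect assumed 82 per group, SD 9.5, about 15% missing T1 and visit correlation 0.6.

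| Relation of missing T1 to outcome | False difference at T1 | Type I error |
|---|---|---|
| None, both services | −0.03 | 5.3% |
| Odds 2.0 times per SD worse, both services | 0.00 (both means up about 1.05) | 5.7% |
| Odds 2.0 times per SD worse, one service only | 1.09 | 11.7% |
| Odds 2.7 times per SD worse, one service only | 1.56 | 18.8% |

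**5. Single imputation, T2 to T4 only.** A missing T1 is never filled in, so the T1 comparison is affected by selection and not by imputation.

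- Level: with 15% LOCF at T4 and recovery still under way, the T4 mean was 6.87 against 7.03 among those observed.
- Standard error: in the same run it averaged 1.48 against an actual spread of 1.52, about 3% low. The other three scenarios showed 0% to 2%. With 3,000 runs the spread itself carries an error of about 1 / √6000 = 1.3%, so the effect is small.
- Upper bound, if filled values carry no information: 1 − √0.85 = 8% at 15% filled, and 1 − √0.80 = 11% at 20% filled.

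**The case against.** The strongest reply is that the documents show neither unequal loss nor its direction. They give one common 15%. Equal selection leaves the difference between services near zero, and adjustment for age, ISS and complications would absorb some selection that acts through severity. This stands: the 1.6 points is a near-worst-case scenario, not an estimate.

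Four stronger readings are tempting, and the documents do not carry them.

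- *The rule selects survivors and treatment responders.* The section mentions neither death nor response. Consent and a rehabilitation indication are required for entry, which may make early deaths uncommon. What the text supports is selection of patients who supply assessments.
- *Discarding for a missing T0 serves no purpose because T0 is unused.* T0 carries age, gender and ISS, which are covariates, and the cost-effectiveness ratio is expressed per improvement on the FIM, which may need a starting value. Missing T0 data do matter, but deleting the patient's follow-up is a poor response.
- *Interpolation is wrong because it uses later outcomes to fill earlier ones.* Multiple imputation and likelihood-based models also draw on later outcomes. The fault is treating a single filled value as observed.
- *Precision is overstated for the powered comparison.* That comparison is at T1, where nothing is imputed.

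A further reply also stands in part. A patient with no follow-up at all contributes no outcome to a T1 to T4 model either, so the proposed analysis would not remove all of the bias sized above. It recovers patients who miss only T0 or T1, and those seen at T1 and then lost.

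**Conclusion.** The point holds for discard-and-replace. The rule is fixed in the article, and nothing elsewhere in it corrects the effect. Three consequences follow from the text without any assumption: inclusion is conditioned on a post-treatment outcome visit, observed outcomes are deleted, and the 15% loss is allowed for a second time.

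A bias between services is possible but conditional. It needs loss that is related to outcome and differs by service, and its direction cannot be known. Its size is about 1.6 FIM points in the near-worst case, 0.8 at correlation 0.5, and near 0 with equal selection.

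The imputation point is secondary and limited to T2 to T4. LOCF holds a patient at an earlier level of recovery at T4, and standard errors are understated modestly: about 3% in simulation at 15% imputed, with 11% as an upper bound at 20%.

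**What to change.** 1. Delete the discard-and-replace rule and keep every enrolled eligible patient.
2. Analyse all observed T1 to T4 outcomes in one likelihood-based repeated-measures model with service, visit, service by visit and the case-mix covariates. Alternatively, use multiple imputation that includes T0 data and those covariates.
3. Impute missing T0 values instead of removing the patient.
4. Keep LOCF and interpolation only as sensitivity analyses, if at all.
5. Add a sensitivity analysis for data not missing at random that includes deaths, because patients with no follow-up remain a source of bias under any of these methods.

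The cost is wording and some extra analysis work; no new visits are needed. Without replacement, 82 enrolled at 15% loss leaves 82 × 0.85 ≈ 70 observed at T1 against the stated 71, with power still about 80%. Retaining 71 would need 84 enrolled per group.

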## Discussion

The main objective of this study is to examine the effectiveness, the costs and the cost-effectiveness of an integrated Supported 'Fast Track' Rehabilitation Service for multi-trauma patients (SFTRS) involving dedicated early rehabilitation intervention programs.

As there are no publications found about contrasts in (cost-) effectiveness between different multi-trauma rehabilitation services it is important to investigate whether a new rehabilitation service is more effective than the conventional service.

During the conceptualisation of the study design several choices had to be made. The major ones will be discussed.

First, randomisation in this study is not possible because of practical and ethical reasons. The distance between the two centres is approximately 150 km. Since this study includes acute (complex) multi-trauma patients who need to be take care of as soon as possible it is not justified to transport patients for hours to accommodate to any randomisation procedure.

Second, in literature the 'severe multi-trauma' patients are frequently reported as having at least 2 or more injuries of which at least 1 is life threatening (ISS > = 16). However, during a pilot study it became apparent that part of the multi-trauma patients suffering from complex multiple injuries and who were admitted to the rehabilitation centre had an ISS < 16. Clinically speaking, it concerned patients suffering from one of the following injuries: a) complex multiple injuries on both lower extremities; b) a combination of one upper and one lower extremity injury, the latter of which could not be used in load-bearing; or c) complex pelvis/acetabulum fractures. Multi-trauma patients, who often suffer from skull and brain injuries, generally have an ISS > = 16. However, especially in complex pathology of the locomotor system, necessitating intensive rehabilitation training, the AIS system often scores less. Given the fact that these patients do participate in CTCS and SFTRS, indicating that they do belong to the target population in accordance with the other inclusion criteria, these patients have been added to the project population. This classification of multi-trauma patients is in accordance with the revised AIS coding ("AIS upgrading") which is currently being elaborated internationally.

In the present study the definition of multi-trauma reads: "Multi-trauma is defined as having at least 2 or more injuries of which at least 1 is life threatening, including a) trauma with ISS > = 16, b) complex multiple injuries on both lower extremities, c) a combination of one upper and one lower extremity injury, the latter of which can not be used in load-bearing, or d) complex pelvis/acetabulum fractures".

In conclusion, this paper describes the design of a prospective, multi-centre, non-randomised clinical trial that will investigate the (cost-) effectiveness of a new Supported Fast Track multi-Trauma Rehabilitation Service (SFTRS). The inclusion of the patients will start in October 2008 and will continue until May 2010. The results of this study will give evidence whether the new 'fast track' rehabilitation service for multi-trauma patients is more effective than the conventional care service, and thus should be introduced nation-wide.

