### Population

Multi-trauma patients admitted to one of the accident & emergency departments (A&E) of the participating hospitals are included. Multi-trauma is defined as having at least 2 or more injuries of which at least 1 is life threatening, including a) trauma with an Injury Severity Scale score ISS > = 16, b) complex multiple injuries on both lower extremities, c) a combination of one upper and one lower extremity injury, the latter of which can not be used in load-bearing, or d) complex pelvis/acetabulum fractures (for in- and exclusion criteria see Table 1)

**Table 1 T1:** Inclusion and exclusion criteria

Inclusion criteria	Age > = 18 years
	Multi-trauma (as defined above)
	Hospitalisation after A&E admission
	Rehabilitation indication, i.e. lasting impairments or handicaps are expected
	Adequate Dutch language skills
Exclusion criteria	Severe alcohol and/or drug abuse
	Severe psychiatric problems

A&E: Accident and Emergency room

Participants for the SFTRS will be recruited in the adherence of the trauma centre in the south of the Netherlands. The reference group will be recruited in the adherence of one of the other trauma centres in the Netherlands. The inclusion of the participants will start in October 2008 and will continue until May 2010. Both medically and ethically it is not feasible to randomise the acute multi-trauma patients across the two trauma centres mainly due to geographical distances. Therefore, a non-randomised controlled clinical trial is used.

Based on the 2005–2007 databases from the participating centres, the influx numbers for the SFTRS group and the CTCS group are expected to amount to about 364/year and 370/year respectively. Prospective data from a pilot study in 2008 showed that, within 3.5 months, in each of the two centres 86 multi-trauma patients were admitted to the A&E. Given an inclusion period of 19 months, approximately 467 patients in each of the respective regions are expected, totalling 934 for this study (see flow chart, Figure 1).

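### Each service is delivered in a single trauma region, so a positive comparison cannot carry the stated step to nation-wide introduction

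*Protocol article*

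**What the plan says.** **Recruitment (Population).** SFTRS patients come from the region of the trauma centre in the south of the Netherlands. For the comparator, "The reference group will be recruited in the adherence of one of the other trauma centres in the Netherlands". The Discussion counts two centres, about 150 km apart, and gives this distance as the reason why patients cannot be randomised.

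**Sample size (Population).** Patients are treated as independent. The calculation aims to "detect a difference of 15% of such improvement in FIM score between SFTRS and CTCS at T1", uses "a common standard deviation (sd) of 9.5", and arrives at "71 persons per group are needed". No allowance is made for variation between centres.

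**Analysis (Statistical analyses).** The section accepts that "variations in case mix between centres can influence the interpretation of outcome data". It answers this with MANCOVAs at T1 to T4, adjusted for age, gender, ISS, number of complications and pre-trauma psychosocial status. All five covariates describe the patient.

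**Conclusion (Discussion, last sentence).** The results are to give evidence on whether the new service "is more effective than the conventional care service, and thus should be introduced nation-wide". The Introduction (general research question and hypothesis) and the Discussion part of the Abstract frame the aim just as generally, as SFTRS against CTCS, without reference to the two regions.

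**The concern.** Service and region are the same variable in this design. A centre term cannot be added to the model, because it would be identical to the service term. A stable centre difference outside the service, such as surgical practice not touched by SFTRS or the way outcomes are rated, therefore enters the estimated service effect in full. Patient-level covariates correct for measured differences in who is treated, not for where they are treated.

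The planned test can thus show that the two regions differ. It cannot show by itself that the service is the reason, or that the same gain would appear in other regions. The closing sentence passes over both steps. At stake is a national policy recommendation that could rest on an ordinary difference between two centres.

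**Working it through.** **1. Inputs from the protocol article (Population)**
- Reference value: "improvement in motor FIM score of 30.2 in a small group of bilateral lower limb multi trauma patients"
- Target difference: 15% of that, 0.15 × 30.2 = 4.53 points
- SD 9.5; two-sided 5% level; power 80%
- 71 evaluable per group; one region per service

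**2. The plan's own figure**

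n per group = 2 × (1.96 + 0.8416)² × (9.5 / 4.53)² = 2 × 7.849 × 4.398 = 69.04, which rounds up to 70. The t-test version gives 70.01, which rounds up to 71. The stated 71 reproduces if patients are independent. Power at 71 per group is then 81%.

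**3. What a fixed centre difference does**

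Suppose that SFTRS has no effect and the centres differ by b FIM points for other reasons. The standard error is 9.5 × √(2/71) = 1.594. The chance of a significant result is Φ(b/1.594 − 1.96) + Φ(−b/1.594 − 1.96).

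| Assumed b (points) | Chance of a significant result, 71 per group |
|---|---|
| 1 | 10% |
| 2 | 24% |
| 3 | 47% |
| 4.53 | 81% |

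More patients do not help. At 467 per group (the number of patients expected per region, not the planned sample), a 2-point difference would be significant 90% of the time.

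**4. What a random centre difference does**

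Now treat the two centres as a draw from a population of centres. The documents give no ICC, so 0.01 to 0.05 is an assumption.
- Between-centre SD = 9.5 × √ICC
- Design effect DE = 1 + (71 − 1) × ICC
- Rejection rate with no service effect = 2 × [1 − Φ(1.96/√DE)]
- 95% half-width for the difference = 1.96 × 9.5 × √(2 × DE/71)

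| Assumed ICC | Between-centre SD | DE | Rejection rate | Half-width |
|---|---|---|---|---|
| 0 | 0 | 1.00 | 5% | 3.1 |
| 0.01 | 0.95 | 1.70 | 13% | 4.1 |
| 0.02 | 1.34 | 2.40 | 21% | 4.8 |
| 0.05 | 2.12 | 4.50 | 36% | 6.6 |

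These half-widths ignore the planned covariates. From an ICC of 0.02 upward they exceed the 4.53-point target.

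**5. Can the trial estimate the missing quantity?**

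No. One region per service leaves zero degrees of freedom for variation between regions. Neither a larger sample nor a different model supplies it.

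**The case against.** **The sentence is conditional.** A reader might infer that the plan has already decided in favour of SFTRS. It has not: it says that the results will bear on whether the service is better. What remains is that it fixes the step from a positive result to national introduction in advance.

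**The design is disclosed and justified.** The article says openly that the trial is non-randomised, explains why, and adjusts for case mix. This stands, and the point does not ask for randomisation. What the article lacks is any statement on centre effects or on how far the result generalises.

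**The trial is called multi-centre, and CTCS is said to be given in several centres.** This does not separate service from region. The reference patients come from one trauma centre's region, and several hospitals inside it would still all lie on one side of the comparison.

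**Some centre differences are the intervention.** A reader might count staffing and local aftercare as contamination. SFTRS is itself a change in the organisation of care, and CTCS is described partly by its varied aftercare, so these differences belong in part to the contrast under study. Surgical practice outside the service and outcome rating are the fairer examples. The documents do not show that either actually differs.

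**The figures rest on assumption.** A reader might take 13% to 36% as the trial's true false-positive rate, or conclude that its planned confidence interval is too narrow. Neither follows. The rates depend wholly on an assumed ICC and on treating centres as random. If the two centres are taken as fixed, the problem is a bias of unknown size. The Statistical analyses section plans tests and names no confidence interval for the outcomes. This objection stands in full, and the figures serve only as illustration.

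**Conclusion.** The point holds as a limit on what may be concluded. The structural part needs no assumption: the Population section and the Discussion place each service in one region, and the planned covariates are all at patient level. The service effect therefore cannot be told apart from a stable centre effect, and the closing inference to national introduction goes beyond the design.

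The numerical part is illustrative. For FIM, with 71 per group, SD 9.5 and an assumed ICC of 0.01 to 0.05, a nominal 5% test would reject about 13% to 36% of the time without any service effect. No such illustration is made for SF-36, because the documents give no SD for it. The planned test remains a usable comparison of these two regional services, subject to residual confounding by patient factors.

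**What to change.** 1. **Discussion, last paragraph:** limit the conclusion to a case-mix-adjusted difference between the two regional services as delivered, and delete the clause on nation-wide introduction.
2. **Discussion, design choices:** next to the explanation of non-randomisation, state as a limitation that service and centre are confounded and that patient-level covariates do not resolve this.
3. **Abstract (Discussion) and Introduction (general research question and hypothesis):** align the general claims on effectiveness and cost-effectiveness with this narrower scope.
4. **Optional:** report beside the FIM result an interval that adds between-centre variance over an assumed ICC range. Label it as a sensitivity illustration driven by assumption, since the trial data cannot inform it.

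Items 1 to 3 cost wording only, and item 4 one calculation. No extra centres or patients are needed, and the planned tests stay as they are. The downside is a less favourable claim.
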